##### Third‐level assessment

In the third-level assessment, CHSWs will accompany ASHA workers to the homes of these recruited patients for performing further detailed assessment. This assessment will comprise standardised tools that assess treatment adherence; medication compliance; and behavioural, social, and cognitive risk factors in patients with chronic illnesses. In addition, this assessment will identify the motivating and protective factors of participants to adhere to treatment and comply with medication. Moreover, DM, HTN, and body mass index (BMI) will be measured by junior public health nurses (JPHNs) in coordination with CHSWs.

#### Human resources for the assessment

ASHA workers will conduct the first-level (verbal screening) and second-level assessments (mobile App based), followed by the detailed baseline assessment performed by CHSWs. Along with ASHA workers, JPHNs will conduct clinical assessments including the measurement of blood pressure (BP) and blood sugar levels. The primary and secondary outcome measurements for determining the effectiveness of the intervention will be performed by a separate group of CHSWs in order to blind the hypothesis from the intervention team. The intervention will be functionally and geographically coordinated by CHSWs appointed in PHCs during the project implementation period.

### Study outcomes

Collection of data at baseline and follow-up at 6 months and 1 year will involve (a) the first-level assessment that includes a survey for collecting information regarding basic sociodemographic factors and verbal screening for examining chronic conditions in potential participants and (b) the second-level assessment that includes the use of standardised questionnaires to collect information on treatment adherence, medication compliance, behavioural risk factors (diet pattern, physical activity, tobacco, and alcohol consumption), social risk factors (perceived social support, neglect, and inclusion), and cognitive risk factors (depression, anxiety, stress), as well as a semi-structured interview schedule for identifying the motivating and protective factors of participants. In addition, trained staff will conduct BP, blood sugar level, and BMI measurements in all participants at three time points (baseline and 6 and 12 months after baseline). Anthropometric measurements will include height (in cm), weight (in kg), and waist circumference (in inches). BP and pulse rate will be measured using electronic BP monitors ([name] BP-02 Blood Pressure Monitor). Trained interviewers used a lancet for finger prick to obtain fresh capillary whole blood and a glucometer to measure the random glucose level. HTN will be measured twice in the sitting position at two time periods, and the average of the two readings will be used as the final value. Detailed survey measures are described in Table 1.

**Table 1 Tab1:** Measurement domains and data collection time points

**Variables**	**Components**	**Measurement Tools**	**Baseline**	**6 months**	**12 months**
Sociodemographic variables		Age, sex, marital status, education, occupation, and family income	✔		
Behavioural measures	Tobacco use, Alcohol consumption, Diet Physical activity	Behavioural and Lifestyle Questionnaire	✔		✔
Cognitive measures	Depression Anxiety Stress	DASS scale	✔		✔
Clinical measures	Anthropometry	Waist circumference (measuring tape) Height (measuring tape) Weight (weighing machine)	✔	✔	✔
	Blood pressure	[name] Pressure Calculator			
	Blood sugar	Glucometer (finger prick method)			
Social measures	Social networks	Wenger’s social network typologies	✔		✔
	Social cohesion	Social cohesion questionnaire			
Treatment adherence	Compliance to medications Adherence to Health check ups	Questionnaire on health service utilisation	✔	✔	✔
Programme evaluation	Group evaluation	Usefulness of group sessions, Utilisation of NGO services	4 month	8 month	12 month
	Other evaluation	Usage of health calendar, diary, etc.	4 month	8 month	12 month

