**Methods:**

A cluster randomised controlled trial (RCT) in selected participants will be conducted involving additional assessments prior to the baseline assessment. The assessment will identify and categorise patients into four risk groups, namely behavioural, social, cognitive, and multiple, based on dominant risks identified. Eligible participants will be randomly allocated (at a ratio of 1:1) into the intervention or control arm. The intervention arm will receive social, behavioural, and cognitive or multiple interventions corresponding to the identified risk groups, whereas the control arm will receive general intervention. Both the groups will be followed up at 6 months and 12 months post baseline to measure outcomes. The primary outcome will be the control of HTN and DM, and secondary outcomes include decreased depression and anxiety and improved functioning, social cohesion, and social network linkages. The sustainability and scalability of this intervention will be assessed through cost effectiveness, acceptability, and user friendliness of the integrated approach by performing a qualitative evaluation.

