### Study design and setting

This is a two-arm cluster randomised controlled trial (RCT) designed to be executed in patients with DM or HTN in association with government-run PHCs and the existing public health ecosystem in Kerala, India. This study will be conducted in Ernakulam district, Kerala, India, with active support from University of York, United Kingdom, and University of Melbourne, Australia. The Ernakulam district is administratively divided into seven main revenue divisions, and Aluva is one of them [14]. The Aluva division is further divided into different units called panchayats (with approximately 25,000–30,000 people residing in each panchayat and each panchayat is further divided into different wards with approximately 1000 to 1500 people residing in each of them), and one panchayat from the Aluva division is selected for the intervention. PHCs and ASHA workers assigned to these geographical units will assist the execution of the intervention. ASHA workers are a network of community health workers who are often selected from the same community; thus, they have the acceptance and trust of the community people. A list of ASHA workers consenting to participate in this study will be prepared, and 10 of them will be randomly selected using computer generated random numbers for providing the intervention. Their assigned wards will be considered as intervention clusters for the current trial. A list of patients with DM or HTN from the selected wards will be obtained from the PHC registry through ASHA workers, and household interviews will be conducted for data collection. Three data collection time points are planned for both the arms: one at baseline and then after 6 months and 12 months after baseline.

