#### Primary outcomes

Primary outcomes include an improvement in risk factor control status (BP < 140/90 mmHg and fasting blood glucose < 110 mg/dL) and abstinence from smoking or tobacco use.

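### The glucose part of the primary outcome is defined on a fasting value, but the only glucose procedure described is a random finger-prick reading

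*Protocol article*

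**What the plan says.** The Primary outcomes section of the protocol article defines risk factor control as "BP < 140/90 mmHg and fasting blood glucose < 110 mg/dL", and lists abstinence from tobacco alongside it. The abstract puts the same aim more broadly: "The primary outcome will be the control of HTN and DM".

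The Study outcomes section describes how glucose is obtained: "Trained interviewers used a lancet for finger prick to obtain fresh capillary whole blood and a glucometer to measure the random glucose level". It also fixes the schedule: "trained staff will conduct BP, blood sugar level, and BMI measurements in all participants at three time points", namely baseline, 6 months and 12 months.

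The other places that mention glucose do not settle its state. Table 1 gives the device and the finger-prick method only. Human resources for the assessment says that "JPHNs will conduct clinical assessments including the measurement of blood pressure (BP) and blood sugar levels", without saying fasting or random. Study design and setting adds that "household interviews will be conducted for data collection".

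**The concern.** A fasting cut-off has its meaning only for a fasting sample. A random reading combines the underlying fasting level with whatever was eaten recently, so whether a patient counts as controlled would depend partly on the hour of the visit.

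This touches the headline outcome. The Statistical analysis section plans adjusted odds ratios for dichotomous outcomes, and for glucose control those would be computed on misclassified data. Because the intervention works on diet, including sugar intake, a difference between arms in random readings could not be read directly as a difference in fasting control. Fasting status that is not recorded at a visit cannot be reliably recovered later, so the matter has to be settled before data are collected.

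**Working it through.** The plan gives no figure to reproduce here. The check is a comparison of statements, followed by an illustration of what the mismatch would do.

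**Step 1: the statements side by side.**

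| Place in the protocol article | Glucose state |
|---|---|
| Primary outcomes (definition) | Fasting, below 110 mg/dL |
| Study outcomes (procedure) | Random, capillary, by glucometer |
| Study outcomes, Table 1 | Not stated |
| Third-level assessment | Not stated (says only that DM is measured) |
| Human resources for the assessment | Not stated |
| Abstract, Methods | Not stated |

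The word fasting occurs only in the definition. No rule converts a random value or sets a different threshold for it. The two explicit statements are incompatible, and no other section reconciles them.

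**Step 2: effect on the arm difference.** Let p be the true proportion with fasting glucose below 110 mg/dL in an arm, and f the share of those patients whose random reading is 110 or above. Suppose first that nobody truly at or above 110 reads below it, and that f is the same in both arms.

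- Observed control in each arm = (1 − f) × p
- Observed difference = (1 − f) × true difference

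The documents give no value for f. With assumed values, and an assumed true difference of 10 percentage points:

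| f (assumed) | Observed difference |
|---|---|
| 0.30 | 0.70 × 10 = 7 points |
| 0.45 | 0.55 × 10 = 5.5 points |
| 0.60 | 0.40 × 10 = 4 points |

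**Step 3: what the two conditions do.**

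- If a share g of uncontrolled patients also read below 110, equally in both arms, observed control is (1 − f)p + g(1 − p). The difference is then multiplied by 1 − f − g.
- If f differs between arms (f₁ intervention, f₀ control) and g is zero, then even with the same true control p in both arms the observed difference is p × (f₀ − f₁), which is bias and not dilution. The documents do not show that this would happen.

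**Step 4: which outcomes are reached.** Blood pressure control and tobacco abstinence do not use glucose. The glucose component does, and so does any status requiring both pressure and glucose to be controlled. The definition does not say whether the two are combined or reported separately.

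**The case against.** The best reply is that the random-glucose sentence may not describe this trial. It is in the past tense while the sentences around it are in the future tense. It names interviewers, whereas clinical measurement is elsewhere assigned to junior public health nurses. It may be carried over from earlier work such as the community survey cited in the Background. This stands as a caution, and for that reason it would go too far to infer that the endpoint cannot be computed. It does not remove the conflict: the sentence sits among the trial's own measurements, and it is the only glucose procedure given.

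A second reply is that fasting instructions and time since last meal are operational details that an article leaves to the full protocol. That is right, and their absence is not counted here. The finding rests on one word against another, random against fasting.

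A third concerns bias between arms. With five wards per arm, a reader might infer that visit timing will differ and distort the comparison. No section says so. Wards are randomised only after baseline is complete, so baseline timing cannot depend on allocation; only follow-up timing could. Bias remains a possibility, not a finding.

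A reader might also infer that half of the control endpoint is lost. The text does not support that share. It does not say how the two parts combine, or whether the glucose part applies to participants who have hypertension alone, who are eligible.

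**Conclusion.** The point holds as a contradiction between two explicit statements about a primary-outcome component, and it must be resolved. It is not a detail that an unseen analysis plan could supply, because no analysis turns a random sample into a fasting one.

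Its size cannot be given from the documents. The shrinkage factor 1 − f assumes misclassification in one direction only and equal in both arms. The values of f from 0.30 to 0.60 are illustrations with no anchor in the text, and the conclusion does not depend on them. The reach is the glucose component and any joint pressure-and-glucose status; the other primary components stand when reported on their own.

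**What to change.** Before baseline collection, reconcile Study outcomes with Primary outcomes so that sample and definition use the same glucose state, in the same way in both arms at baseline, 6 and 12 months. Which state is intended is for the trial team to say. There are two workable routes:

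- **Keep the definition.** Collect the finger-prick sample fasting, record fasting status on the form, and correct the sentence on random glucose. The cost is morning scheduling: with 1452 participants and three visits, up to 1452 × 3 = 4356 fasting visits.
- **Keep random sampling.** Restate the glucose outcome as random glucose, analysed as a continuous variable adjusted for its baseline value, with the same visit-time window in both arms. Record time since last meal, but use it only in a sensitivity analysis: at follow-up it is measured after randomisation, and an intervention on diet and family routines could change it, so adjusting for it in the main analysis could itself introduce bias. The cost is a changed primary-outcome component, which must be notified to the review board and updated in the trial registration.

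Under either route, state whether pressure and glucose control are reported separately or as one status.

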#### Primary outcomes

Primary outcomes include an improvement in risk factor control status (BP < 140/90 mmHg and fasting blood glucose < 110 mg/dL) and abstinence from smoking or tobacco use.

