### Participant recruitment and study procedure

Participants for the trial will be recruited according to eligibility criteria. Eligible families will be those with at least one family member with a confirmed diagnosis of HTN and/or DM. The medical records of the patient will be used to confirm the diagnosis. Informed consent will be obtained from all adult family members. In addition, family members must be either first-degree blood relatives or spouses of the patient. Bedridden and terminally ill patients will be excluded from the study. Participation will be completely voluntary and can be withdrawn at any point if they intent to.

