### Statistical analysis

Data will be analysed on the basis of the intention to treat principle. Changes observed from the baseline and at follow-up will be compared between the intervention and usual care groups. All data will be de-identified using a unique ID to ensure the confidentiality of information. Upon implementation of the intervention, follow-up measurements will be taken at 6 and 12 months from the baseline. Data will be generated from standardised questionnaires and assessment procedures. Baseline characteristics will be described using means (with standard deviations) or frequencies based on the type of variable. The mean difference between the groups will be examined to understand the effects of the intervention. Mixed effect analysis of covariance will be employed to test for interactions between time (pre and post) and group (intervention or usual care), and partial eta squared (ηp^2^) will be reported as a measure of effect size. The comparisons of variables will be adjusted for potential confounders. The intention-to-treat analysis will be used to observe changes occurred throughout the year during follow-up in participants assigned to the Swāsthya intervention and usual care. The effect attributable to the intervention will be estimated by calculating mean differences between the groups at each of the follow-up points (at the baseline and at 6 and 12 months after the baseline; adjusted odds ratios for dichotomous outcome variables at 95% confidence intervals). Precautions will be taken to rule out the potential interaction effects between the Swāsthya and usual care groups. Software-assisted multiple imputation methods up to five times will be used to deal with missing values. All statistical analyses will be performed using STATA-14 and R software. The effectiveness of the intervention model will be ascertained 1 year after the completion of the study, and the model in itself will also be made public. Information on the study will be available on the website of the college as well as reported in scientific journals and at scientific conferences.

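### The primary outcome differs between abstract and body and is not fixed: its components, its visit and the patients to whom each limit applies are left open

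*Protocol article*

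**What the plan says.** The Methods paragraph of the abstract is in the singular: "The primary outcome will be the control of HTN and DM, and secondary outcomes include decreased depression and anxiety". Tobacco is not mentioned there.

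The Primary outcomes section is in the plural and opens an inclusive list: "Primary outcomes include an improvement in risk factor control status (BP < 140/90 mmHg and fasting blood glucose < 110 mg/dL", continued by "and abstinence from smoking or tobacco use".

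Eligibility, under Participant recruitment and study procedure, is by either disease: "Eligible families will be those with at least one family member with a confirmed diagnosis of HTN and/or DM". It requires neither uncontrolled disease nor tobacco use at entry.

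Under Statistical analysis, effects are to be estimated as "mean differences between the groups at each of the follow-up points", with "adjusted odds ratios for dichotomous outcome variables at 95% confidence intervals". No visit is singled out, and baseline is itself listed among the follow-up points. The population rule is "Data will be analysed on the basis of the intention to treat principle".

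On timing, the Study outcomes text includes tobacco in the data gathered at baseline, 6 months and 1 year. In Table 1 the behavioural row ("Tobacco use, Alcohol consumption, Diet Physical activity") is ticked at baseline and 12 months only. The same text says that the glucometer reading is a random one, whereas the primary outcome is defined on a fasting value.

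**The concern.** A confirmatory trial needs one answer to the question of what has to be shown, when and in whom. Here the reader gets different answers from different sections. Tobacco is absent from the primary outcome in the abstract and part of it in the body. In the third objective under Aim of the study, smoking is one of the behaviours through which blood pressure and diabetes are meant to change.

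Three things are at stake. First, whoever writes the report could choose the primary result (control, a single limb of control, or tobacco, at 6 or 12 months) after seeing the data. Second, the joined control rule would score single-condition patients on a disease they do not have. Third, tobacco abstinence counted over everybody includes people who never used tobacco and already meet the criterion.

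**Working it through.** **1. What is primary, set side by side.**
- Abstract: one outcome, control of the two diseases.
- Primary outcomes section: blood pressure and glucose control, plus tobacco abstinence, in an open list.
- Statistical analysis: every follow-up point, none ranked; the mixed model is described as pre and post although there are three visits.

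These support at least three readings: two outcomes (joint control; tobacco), three outcomes (blood pressure; glucose; tobacco), or one composite.

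**2. Does the sample size show which reading was meant?** The plan's figure is 1452 (726 per arm), and the only rate given is a 36.33% community prevalence of hypertension and/or diabetes. A single-proportion precision formula gives 1.96² × 0.3633 × 0.6367 / 0.035² = 725.4, rounded up to 726, but only with an unstated precision of 3.5 points. A two-arm comparison of 36.33% with a rise of 8.33 points at 90% power gives 728, also on unstated choices. The match is not unique, and a prevalence is not a control or quit rate. The sample size therefore does not identify the primary outcome.

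**3. Error if any one success counts.** Assume two-sided 5% per test (implied by the 95% intervals) and independence. Family-wise error = 1 − 0.95^k.
- k = 2 (control, tobacco, at 12 months): 1 − 0.9025 = 9.8%.
- k = 3 (blood pressure, glucose, tobacco, at 12 months): 1 − 0.8574 = 14.3%.
- k = 5 (blood pressure and glucose at both visits, tobacco at 12 months as in Table 1): 1 − 0.7738 = 22.6%.

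Positive correlation lowers these. In a simulation of three tests (1,000,000 draws) the error is 13.6%, 12.5% and 9.9% at correlations of 0.3, 0.5 and 0.8. If all outcomes must succeed, the error does not exceed 5%.

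**4. The joined limits.** Entry is by either disease or both; the control rule connects the two limits with a plain conjunction; blood pressure and blood sugar are measured in all participants. Nothing exempts a patient with hypertension alone from the glucose limit, or one with diabetes alone from the blood pressure limit.

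**5. Tobacco in all participants.** Let u be the share of tobacco users at baseline, which the document does not give. If non-users stay abstinent in both arms, the overall difference is u × the difference among users. For illustration, assume abstinence of 30% versus 40% among users, 726 per arm and no clustering:

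| u (assumed) | Difference, all participants | Power, all participants | Power, users only |
|---|---|---|---|
| 0.1 | 1 point | 12% | 24% |
| 0.2 | 2 points | 20% | 43% |
| 0.3 | 3 points | 30% | 59% |

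Clustering lowers every power figure. With an assumed ICC of 0.01 and about 145 patients per ward, the row for u = 0.2 becomes 11% and 35%.

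**The case against.** The best defence is that this is a journal article. A multiplicity method, analysis denominators and the covariate list commonly sit in a statistical analysis plan, and their absence here is no fault. That stands, and the point does not rest on it. It rests on statements that are present and disagree: abstract against body on what is primary, text against table on when tobacco is recorded, and a joined rule against an either-disease entry criterion.

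Stronger readings are tempting, and the document does not support them.

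- A reader might infer that patients who cannot improve, or who never smoked, are credited with success. No section says how they are scored. Taken literally, improvement would deny credit to a patient already controlled at entry. The scoring is undefined, not shown to be wrong.
- A reader might infer that the type I error is inflated. That follows only if success on any one outcome suffices, and the document does not say so.
- A reader might count three outcomes at two visits and quote 1 − 0.95^6 = 26%. That needs the 6-month tobacco data that Table 1 omits, as well as independence between repeated measures on the same patients.
- A reader might argue that patients controlled at entry dilute the control outcome by their full share. They can lose control, so they are not patients without a possible effect, and keeping control is part of what the trial seeks.

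On tobacco, adjustment for confounders is planned. If baseline use is among the covariates, the odds ratio is largely protected. The absolute difference over all participants is not.

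**Conclusion.** The point holds as a contradiction and an unfixed primary outcome. Four things follow from the text with no assumption: tobacco is primary only in the body; the components have no stated relation and no primary visit; the blood pressure and glucose limits are joined although patients may have only one of the diseases; and the 6-month tobacco assessment is in the text but not in Table 1.

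The size is conditional. Family-wise error would be 9.8%, 14.3% or 22.6% for two, three or five independent tests under an any-success rule, less with positive correlation, and not inflated at all if every outcome must succeed. The absolute tobacco difference over all participants shrinks in proportion to the share of non-users, which is unstated; the figures of 1 to 3 points rest on assumed rates. A proven error rate, or a proven dilution of the control outcome, cannot be claimed from this document.

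**What to change.** - State one primary outcome at 12 months: the proportion controlled for the condition(s) the patient entered with (blood pressure limit if hypertension, glucose limit if diabetes, both if both), adjusted for baseline control status. Make 6 months secondary.
- Either make tobacco abstinence secondary, or keep it primary beside control with Holm at 12 months. In both cases analyse it in those using tobacco at baseline. Baseline data are complete before the wards are randomised, so this group is defined free of allocation.
- Align the abstract, Primary outcomes, the Study outcomes text, Table 1 and Statistical analysis, including the 6-month tobacco entry.
- Reconcile the fasting glucose in the outcome definition with the random glucose described under Study outcomes. Until that is done, the glucose limit cannot be scored as defined.

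The cost is mainly wording, in the protocol and the registry entry, to be settled before outcomes are compared by arm. Tobacco loses primary status, or alpha is shared. With two outcomes, Holm's first step is at 0.025; for 80% power at that step (an assumed target) the sample size rises by (2.241 + 0.842)² / (1.960 + 0.842)² = 9.505 / 7.851 = 1.21, about 21%. Because 1452 is not tied to a stated effect on any outcome, its power for the chosen outcome should be stated anew, allowing for the 10 wards.
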